### Trial design {8}

This is a prospective, multicenter, two-armed, active-controlled, parallel group, randomized controlled superiority trial that will be conducted at eight university outpatient psychotherapy centers in Germany. A total of 250 adult patients with SSD will be included, 125 patients per study arm. Participants will be randomly allocated to the two conditions. Both study groups receive 20 sessions of CBT. Additionally, the intervention group receives the iSOMA internet intervention, while the active control group receives a self-help booklet. Primary and secondary outcomes will be measured before randomization (baseline), during the course of treatment, after completion of the face-to-face treatment (post-assessment), and 6 months after end of treatment (follow-up) (see Fig. 1).

**Fig. 1 Fig1:**
[figure not shown]
Study flow chart

## Methods: participants, interventions, and outcomes

This protocol manuscript follows the SPIRIT reporting guidelines and the SPIRIT checklist is attached [42].

### Study setting {9}

Eight German university outpatient clinics for psychotherapy will serve as study centers, based at the Johannes Gutenberg University Mainz, Central Institute of Mental Health, Medical Faculty Mannheim/University of Heidelberg, Philipps University Marburg, RPTU University Kaiserslautern – Landau, Ulm University, Bergische University Wuppertal, University of Konstanz and Psychologische Hochschule Berlin. All centers are involved in patient recruitment and the implementation of study therapies. In all centers, treatment will be offered in an outpatient setting.

### Eligibility criteria {10}

Adults (≥ 18 age) diagnosed with SSD (according to DSM-5) who also exhibit a sufficient level of symptom severity, as indicated by a score ≥ 5 in the Patient Health Questionnaire, somatic symptom version (PHQ-15 [43]), and disability, as indicated by a score ≥ 4 in the (modified) Pain Disability Index (PDI [44]), and who have access to the internet and an internet-capable device, will be eligible for inclusion. The selected PHQ-15 cut-off has been shown to be a suitable marker for identifying individuals at high risk for a diagnosis of SSD in a representative population sample [45]. Similarly, the PDI cut-off has proven to be sensitive to relevant impairments in functional status due to PSS in a population-based survey [44]. Prior to their inclusion in the study, written informed consent will be obtained from all participants (inclusion criteria). Participants who meet at least one of the following exclusion criteria will be unable to enroll in the trial (exclusion criteria): (a) Acute, unstable, or severe physical condition that prevents safe trial participation, (b) inadequate command of the German language (reading and/or speaking) (c) severe substance use disorder (according to DSM-5), (d) acute suicidality or (e) acute psychotic states, (f) parallel psychotherapy or (g) participation in another intervention study. The study therapists will be licensed CBT therapists or clinical psychologists currently undergoing advanced post-graduate CBT training under supervision. Prior to treating study patients, all therapists will complete study-specific training provided by the principal investigator (PI) about SSD, the treatment conditions, and the study procedures. For ethical considerations, the study does not include a no-treatment control group.

### Who will take informed consent? {26a}

Individuals who are potentially eligible and interested after pre-screening are invited to participate in an interview with an independent, trained clinical psychologist from the study team. During this interview, the participants are informed in detail about the study and will be given time and opportunity for questions and concerns. The information is provided in both verbal and written formats. The following aspects are explained: (a) the objective of the study and its scientific relevance, (b) the procedure and duration of participation in the study, (c) potential risks or side effects, (d) possible benefits, (e) collection and processing of study data (including data security), and (f) the right to terminate participation in the study at any time without giving reasons and without negative consequences. Eligible participants who are willing to participate will then sign informed consent. The informed consent materials and forms are available from the corresponding author on request.

### Additional consent provisions for collection and use of participant data and biological specimens {26b}

Not applicable, the trial does not involve collecting biological specimens.

## Interventions

### Explanation for the choice of comparators {6b}

The intervention group (blended psychotherapy) will be compared to an active psychotherapy control group. CBT is considered a standard, theory- and evidence-based psychological treatment in outpatient or multidisciplinary inpatient settings [16, 19, 20, 46, 47]. In the control group, CBT will be combined with self-help bibliotherapy. Previous studies have demonstrated positive effects of bibliotherapy, but these have predominantly focused on functional somatic syndromes [48], indicating a research gap for the broader diagnostic spectrum of SSD. For instance, Hedman et al. [49] found comparable effects between bibliotherapy and internet-based CBT in reducing health anxiety among patients with SSD and illness anxiety disorder. However, this study exclusively targeted health anxiety and bibliotherapy was implemented as stand-alone treatment, without integration into face-to-face therapy. In the current study, the structure, content and dosage of the bibliotherapy (consisting of 7 chapters) will be practically matched to the supplementary internet intervention (7 consecutive modules), allowing differentiation between effects due to delivery format and those due to treatment dosage. In case of ethical requirements (e.g., crisis intervention), participants in both study groups may receive up to four additional “joker sessions” on top of the manualized sessions. Likewise, continuation of treatment beyond the study therapy may be permitted based on clinical judgment for ethical reasons and will be monitored accordingly. Nonetheless, the superiority of blended psychotherapy is assumed, given the multimedial and interactive design as well as further persuasive, that is, engagement-enhancing, features of iSOMA (i.e., automatic reminders, progress bar, unlocking achievements), compared to passive bibliotherapy [50].

### Intervention description {11a}

In both conditions, patients receive health insurance-covered outpatient individual psychotherapy, based on an established and efficacious CBT manual for PSS and somatoform disorders [51–53]. Therapy sessions take place on an approximately weekly basis, and overall treatment duration is thus estimated with a minimum of 6 months (including possible intervals). The therapeutic concept targets characteristic perpetuating cycles between cognitive, behavioral, and physiological responses that maintain symptoms, distress, and disability according to cognitive-behavioral and somatosensory models of PSS [54, 55]. An overarching goal of the treatment is to enhance patients’ motivation to explore further biopsychosocial explanations for their bodily symptoms and to identify self-efficacious strategies for reducing and managing symptoms and functional disability. Cognitive modifications include reducing selective attention to bodily processes by fostering greater flexibility in perception and experience, broadening symptom attributions and developing constructive evaluation patterns in response to symptom experiences (e.g., changing expectations or self-instructions), as well as promoting a realistic, dimensional understanding of illness and health. On a psychophysiological level, the treatment seeks to lower autonomic arousal through regenerative stress management techniques, particularly by relaxation training. Behaviorally, the treatment aims to reduce illness behaviors by developing physical resilience and balanced activity level, helping patients to replace maladaptive patterns such as avoidance or protective inactivity, and excessive safety behaviors (e.g., medical reinsurance) [52, 53]. An overview of the treatment protocol is given in Table 1.

**Table 1 Tab1:** Overview of treatment sessions

Regular psychotherapy	Treatment content	iSOMA online modules/self-help booklet chapters
Session 1–2	Symptom monitoring, goal setting	My compass
Session 3–4	Education on stress reaction (e.g., autonomous nervous system, symptom influence), relaxation exercises	Stress and the body
Session 5–7	Attention modification, behavioral activation	Shifting focus
Session 8–12	Cognitive restructuring	Changing perspectives
Session 13–16	Reduction of illness behavior (e.g., reinsurance-, safety, avoidance behavior), graded physical exercise	Finding strength
Session 17–19	Stress management, education on transactional stress model, stress-coping, communication skills	Solving problems and strengthening relationships
Session 20	Summary and self-management	Fit for the future

*Intervention group (blended psychotherapy):* In addition to the face-to-face treatment protocol, participants receive the accompanying internet intervention (iSOMA), consisting of seven modules and a technical introduction. Thus, iSOMA mirrors a chronological, mostly standardized self-help intervention. The content and scheduling of the iSOMA modules are tailored to the face-to-face session protocol and show a high degree of content overlap, reinforcing treatment transfer and multimodal learning (see Table 1). Each of the iSOMA modules includes standardized elements of psychoeducation, exercises, behavioral experiments, and assignments, which are presented in a multimedia format via text, audio, or video in an interactive form (e.g., free text fields for personal experience, preset feedback for multiple-choice questions, quizzes). Fictional patient examples (e.g., gastrointestinal, pain-related symptomatology, avoidant or endurance type) are used to illustrate typical problems and therapeutic principles. In addition, persuasive design features such as automatic reminders, tailored progress tracking and aspects of gamification (e.g., achievable skills) are incorporated. The modules can serve both as primers and enhancements of face-to-face sessions and are activated consecutively by therapists within the corresponding treatment sections, thus following a semi-flexible integration mode, which for example was recently studied in outpatient psychotherapy for depression and anxiety as part of the PSYCHOnlineTHERAPIE trial [56]. The ratio of treatment sessions to digital modules is approximately 3:1 (see Table 1). Patients work through the content between sessions using their own devices (e.g., PC, laptop, tablet, smartphone), while having the option to save their progress intermittently. Therapists can monitor the patient’s progress in the online modules and are encouraged to integrate content such as digital worksheets and exercises into treatment sessions. While initial contact via the platform is technically possible for therapists, it is neither intended nor permitted as part of the study protocol. According to the findings of preceding studies [57], the estimated processing time for each online-module ranges from approximately 45 to 60 min. iSOMA builds on a previously evaluated intervention form, tested as a guided, cognitive-behavioral, modular online program for PSS (non-blended). In a randomized controlled trial with 156 emerging adults (mean age 24 years, 83% female), iSOMA led to significantly greater reductions in somatic symptom severity (PHQ-15: *d* = 0.70) and SSD-related distress (SSD-12: *d* = 0.65) compared to a waitlist control group [57]. In a subsample with clinically relevant levels of self-reported somatic symptom distress (*n* = 83), similar effects than for the total sample were observed (PHQ-15: *d* = 0.68; SSD-12: *d* = 0.72). The implementation of the internet intervention utilizes the university-based, open-source eHealth platform “eSano”, which was developed by a member of the trial steering team (HB) and IT-expert (RP) [58, 59]. The platform was developed with consideration of the regulatory frameworks defined by the German Medical Devices Act and the European Union Medical Device Regulation. The software development and validation process was guided by internationally recognized standards, including IEC 62304 (classified as safety class B), GAMP5 (category 4), the FDA's General Principles of Software Validation, and the Pharmaceutical Inspection Co-operation Scheme guideline 11-3 [56].

*Control group:* In addition to the face-to-face treatment protocol, patients receive a self-help booklet, corresponding to the structure and content of the online modules (see Table 1). It contains information material, exercises, and worksheets intended for self-help. The booklet is handed out by therapists at treatment initiation (visit 4, see Fig. 2).

### Criteria for discontinuing or modifying allocated interventions {11b}

In the event that clinical circumstances arise during treatment that render continuation of the allocated intervention inappropriate, unsafe, or a strictly manualized approach ethically untenable, the therapist and supervisor (see subsequent section) may jointly decide to discontinue or modify the intervention and continue treatment within routine care. Such circumstances may include acute suicidality, acute psychotic symptoms, severe psychological or physical deterioration, withdrawal of consent by the participant, parallel psychotherapeutic treatment, enrolment in another clinical trial or research project that is not scientifically or medically compatible with the present study, or persistent non-compliance with treatment or study procedures that precludes protocol-compliant participation. Participants may discontinue the intervention at any time without providing a reason and without any disadvantages. Participants are invited to post-treatment assessment and the follow-up assessment even in case of intervention discontinuation.

### Strategies to improve adherence to interventions {11c}

Both interventions are manualized, and therapists will be trained in both treatment forms. All treatments are video- (or audio-)taped and - in case of trainee therapists - continuously supervised (approximately every fourth session) by licensed supervisors experienced in the CBT rationale [51]. Licenced psychotherapists will schedule regular intervision groups. Adherence and engagement with the online modules will be automatically assessed within the platform. Therapists can monitor their patients’ platform usage (e.g., lecture/diary completion) and address potential issues in personal sessions. In the control group, patients will report their use of the self-help booklet regularly during the treatment process. Treatment integrity will be video- (or audio-)registered and rated after completion of the treatments using the method of assessing treatment delivery (MATD) in clinical trials [60]. Although therapists deliver both treatment forms, treatment contamination can practically be ruled out since therapists cannot alter the add-on (iSOMA vs. self-help booklet). Patients in the intervention group receive automatic e-mail notifications if a new module has been assigned to them or if they have not completed a module within ten days.

### Relevant concomitant care permitted or prohibited during the trial {11d}

If suicidality requires acute treatment (e.g., referral to inpatient treatment), patients will be excluded from this trial, and these events will be monitored. Additional psychotherapy is not allowed. In principle, all other forms of treatment (except parallel psychotherapy) are permitted, including the use of medication, as this reflects the reality of clinical practice. Accompanying treatments are recorded and changes are regularly monitored (see Fig. 2).

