*Secondary outcomes* will be assessed at baseline, post-treatment and at the 6-month follow-up and will include the following constructs and questionnaires: adverse psychobehavioral consequences of somatic symptoms (Somatic Symptom Disorder – B Criteria Scale, SSD-12 [73]), symptom coping (Pain Coping Questionnaire, FESV, coping subscales [75]), health related self-efficacy (Pain Self-Efficacy Questionnaire, FESS [79]), depression (Patient Health Questionnaire – depression scale, PHQ-9 [74]), anxiety (Generalized Anxiety Disorder, GAD-7 [76]), health anxiety (Whiteley Index, WI [77]), disability (Pain Disability Index, PDI [44]), quality of life (World Health Organization Quality of Life questionnaire, WHOQOL-BREF [78]), and experience in personal social systems (Experience in Personal Social Systems Questionnaire, EXIS.pers [64]). *Mediators* of treatment effects will include self-efficacy (assessed via FESS), treatment agency (assessed via the therapy-oriented processing subscale of the Therapeutic Agency Inventory, TAI [39, 65]), and disability (assessed via PDI). Mediators will be assessed at baseline, during treatment (sessions 1, 5, 10, 15), post-treatment, and at follow-up. *Potential moderators* of the treatment-related change processes will be explored. These will be assessed at baseline and will include (a) demographic variables, (b) clinical characteristics (e.g., comorbidity, baseline symptom severity, traumatic experience via the Childhood Trauma Screener (CTS [63])), and (c) treatment characteristics (e.g., parallel treatments, type of referral, preferences, treatment expectations assessed via the Generic rating scale for previous treatment experiences, treatment expectations, and treatment effects (GEEE [68])). Health care utilization (Health care Utilization Questionnaire, HCU [80]) will be assessed at baseline, post-treatment and at follow-up. In addition, therapist behavior and therapeutic alliance will be assessed during treatment (sessions 1, 5, 10, and 15) using the Warmth & Competence Scale (W&C [69]) and the Working-Alliance Inventory – short revised (WAI-SR [72]). General treatment satisfaction will be assessed post-treatment using the Client Satisfaction Questionnaire (ZUF-8 [81]), and module-specific satisfaction and perceived effectiveness of iSOMA will be assessed using self-constructed items. The extent to which iSOMA is a normal part of the daily working routine of therapists will be assessed post-treatment with the Normalization Measure Development questionnaire (NoMAD [67]). In both study conditions, adherence and duration of intervention use will be continuously monitored throughout the treatment period using self-constructed items. Self-rated negative treatment effects will be assessed post-treatment by the Negative Effects Questionnaire (NEQ [66]). Psychotherapists will provide sociodemographic data and indicate treatment preference at baseline and monitor SAEs and events of special interest (ESIs) and protocol deviations throughout treatment (sessions 1, 5, 10 and 15), post-treatment and at follow-up (administered by study personnel).

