
### Participant timeline {13}

Individuals expressing interest will be subjected to a telephone (or in-person) interview to determine preliminary inclusion and exclusion criteria (pre-screening), accompanied by filling out questionnaires for screening purpose (basic patient data, PHQ-15, PDI). Preliminary eligible individuals will then be invited to a personal informational interview. During the course of the interview, the participants will be provided with comprehensive information and written consent will be obtained. The diagnosis of SSD will be confirmed based on the Diagnostic Interview for Psychological Disorders (DIPS; [61]), which will be administered by independent, experienced therapists. If eligibility criteria are met and the patient agrees to participate by signing the informed consent, they will be asked to complete the baseline survey (t0). Afterwards, participants will be assigned to their study therapist and the regular, health insurance-covered therapy regimen will continue, starting with up to four probatory sessions. In the initial two probatory sessions, which are mandatory preliminary appointments in the German health care system to assess diagnosis, treatment indication, and therapeutic fit, the study therapists will continue the diagnostic process using the short form of the diagnostic interview (Mini-DIPS; [62]) to assess potential exclusion criteria (SSD not main diagnosis) or further comorbid diagnoses. Patients will be referred for routine care medical check-up (“Konsiliarbericht”) to identify medical red flags that prevent safe trial participation. In cases of uncertainty, a medical supervisor will be available for consultation regarding the clarification of potential red flags. If all inclusion criteria are fulfilled, participants will be randomly assigned to one of the two study arms automatically within the electronic database (randomization, allocation). In the third probatory session, participants in the intervention group will be granted access to iSOMA, while those in the control group will be provided with the self-help booklet. Patients will then receive 20 sessions of blended psychotherapy or enhanced psychotherapy, respectively, in accordance with the session protocol depicted in Table 1. At therapy sessions 1, 5, 10, and 15, the primary outcome and putative mediators will be assessed (paper-based or digitally). In addition, the therapists will document changes in concomitant treatments (e.g., medical treatments), SAEs/ESIs that could influence the study therapy, and actions taken (e.g., after consultation with supervisor and/or study head). At the end of treatment (after 20 sessions, regular end of therapy or discontinuation of therapy), participants will complete the post-treatment assessment (paper-based or digitally). Therapists in the blended psychotherapy condition will also complete a brief questionnaire assessing their experience with the implementation of the online platform into treatment. Patients will be invited to a diagnostic telephone interview administered by the study personnel. Six months after the end of treatment, patients will complete a follow-up survey (paper-based or digitally) and will also be invited to another diagnostic interview via telephone. Figure 2 presents the participant timeline and the scheduling of the assessments.

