### Adverse event reporting and harms {22}

Psychotherapy is generally considered safe, even though discussing personal issues can sometimes evoke strong or unpleasant emotions. The researchers do not anticipate any excess risks or negative effects for participants from the treatment or study procedures. Participants will receive high-quality outpatient psychotherapy and complete established, standardized questionnaires. There will be no special physical demands on study participation (no blood or saliva sampling, no medication or placebo administration, no invasive measurements). Potential side effects of the treatment will be systematically assessed throughout the trial by therapists using a checklist at the time of occurrence and during scheduled visits (sessions 1, 5, 10, and 15) as well as at the post-assessment and the follow-up assessment (administered by study personnel). This is done to monitor any SAEs or events that may negatively influence the course of treatment. The following SAEs will be assessed systematically: (1) death, (2) attempted suicide, (3) intentional self-injury, (4) intoxication with a psychotropic substance requiring medical treatment, (5) life-threatening event, (6) unplanned hospitalization, (7) persistent or significant disability or incapacity. In addition to SAEs, certain ESIs will also be recorded, even if they do not meet any of the above-mentioned criteria for seriousness. These include the following: suicidal ideation or plans, the development of an acute psychosis, and the breakdown of a close or important relationship. Therapists are instructed to discuss all these events and potential subsequent actions in supervision. Additionally, patient-rated potential side effects of the treatment will be assessed via standardized self-report (NEQ) at post-assessment.

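### The rule on suicidality that needs acute treatment excludes the patient from the trial, while the discontinuation rule only stops therapy and keeps the assessments; for randomised patients the plan should say that assessment continues

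*Protocol article*

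**What the plan says.** Two sections of the Protocol article address a patient who becomes acutely suicidal.

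- **Relevant concomitant care {11d}:** "If suicidality requires acute treatment (e.g., referral to inpatient treatment), patients will be excluded from this trial, and these events will be monitored".
- **Criteria for discontinuing or modifying allocated interventions {11b}:** therapist and supervisor "may jointly decide to discontinue or modify the intervention and continue treatment within routine care. Such circumstances may include acute suicidality", among other grounds. The section closes with a retention rule: "Participants are invited to post-treatment assessment and the follow-up assessment even in case of intervention discontinuation".

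Three further places bear on the point.

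- **Participant timeline {13}** treats stopping therapy as one way of reaching t1: "At the end of treatment (after 20 sessions, regular end of therapy or discontinuation of therapy), participants will complete the post-treatment assessment". It adds, for t1, "Patients will be invited to a diagnostic telephone interview administered by the study personnel", with a second such interview at six months.
- **Outcomes {12}** defines the intention-to-treat (ITT) population as every randomised patient.
- **Eligibility criteria {10}** lists acute suicidality as exclusion criterion (d), which governs entry.

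**The concern.** Suicidality that needs acute treatment is a case of acute suicidality, so both rules can apply to the same randomised patient. The {11d} rule is mandatory and is worded at the level of the trial. The {11b} rule is discretionary, is worded at the level of the intervention, and keeps the later assessments. No section says that exclusion in {11d} means only the end of study therapy. A site that follows {11d} to the letter could stop collecting data on a randomised patient because of an event related to outcome, while another of the eight sites follows {11b} and continues.

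Safety follow-up has the most to lose. Objectives {7} includes comparing serious adverse events and side effects between arms, and the patients affected are those whose later course matters for that comparison. The background section itself notes that suicidality often accompanies the disorder, so the situation is foreseeable.

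**Working it through.** No figure in the plan is in dispute. The check sets the rules side by side and then counts what depends on the reading.

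**Step 1. Compare the rules for a randomised patient whose suicidality needs acute treatment.**

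| Question | {11d} | {11b} and {13} |
|---|---|---|
| Does study therapy stop? | Yes, mandatory | May be stopped or modified, by joint decision |
| Are t1 and follow-up offered? | Not stated; literally no, since the patient is out of the trial | Yes |
| Is the triggering event recorded? | Yes | Yes, under {22} |

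The first row can be harmonised: {11d} is a stricter sub-rule for a narrower case. The second row cannot be settled from the text.

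**Step 2. Count the assessments that depend on the second row.** The case is a randomised patient excluded before t1. Counts are from {12}, {13} and {22}.

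- SOMS-7R: baseline + sessions 1, 5, 10, 15 + t1 + follow-up = 1 + 4 + 1 + 1 = 7 time points. At stake: t1 and follow-up, 2 of 7.
- Diagnostic interviews after randomisation by study personnel: t1 + follow-up = 2. At stake: 2 of 2.
- Negative Effects Questionnaire (NEQ): t1 only = 1. At stake: 1 of 1.
- Scheduled checks for serious adverse events and events of special interest: sessions 1, 5, 10, 15 by therapists + t1 + follow-up by study personnel = 4 + 2 = 6. At stake: 2 of 6, the only two made by study personnel.
- Secondary questionnaires: SSD-12, FESV, FESS, PHQ-9, GAD-7, WI, PDI, WHOQOL-BREF, EXIS.pers = 9. According to {12}, they "will be assessed at baseline, post-treatment and at the 6-month follow-up and will include the following constructs and questionnaires". Only FESS and PDI are also measured in sessions, as mediators. So 9 − 2 = 7 would have no post-baseline value at all.

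**Step 3. Separate this from the loss due to stopping therapy.** The counts are losses additional to those from stopping therapy; they are not total losses. A patient who stops after session 5 also lacks the session 10 and 15 values, under either rule. The t1 and follow-up items are the part specific to the {11d} wording.

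**Step 4. Consider the primary analysis.** The mixed model uses all available observations, so SOMS-7R values already collected in sessions remain in it, provided the patient reached session 1. Sample size {14} allows up to 20% drop-out at t1: 0.20 × 250 = 50 patients, leaving the 200 required. The documents give no rate for these events, so neither a number of affected patients nor a bias can be derived.

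**The case against.** The strongest reply is that the governing section already answers the question. {11b} is where stopping an intervention is regulated, it names acute suicidality, and its retention rule is unqualified. {13} makes discontinuation a trigger for t1. {11d} deals with concomitant care and never says that assessments stop or that data are discarded. On this view, exclusion is loose wording for coming off study therapy. The article also condenses a fuller protocol, where leaving therapy and leaving the study may be distinguished.

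Much of this stands. The two sections do not contradict each other on whether therapy ends; what is left is an ambiguity about data collection. The triggering event is not lost either: {11d} says it is monitored, and {22} has events recorded "by therapists using a checklist at the time of occurrence and during scheduled visits (sessions 1, 5, 10, and 15").

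The reply does not remove the point. {11d} says the trial where {11b} says the intervention, and it is the more specific and mandatory of the two. The entry criterion does not explain it, because {11d} concerns care during the trial. Nor is this detail left to another document: the rule is stated here, and stated in a way that conflicts with the retention rule.

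A reader might infer more: that these patients drop out of the ITT set, that the trial loses power, or that the primary result is biased. The documents support none of these. The ITT definition covers every randomised patient and {11d} does not amend it. The drop-out allowance already covers losses at t1. Without an event rate, no bias can be put in numbers.

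**Conclusion.** The point holds as a minor one. For a randomised patient whose suicidality needs acute treatment, the plan does not settle whether assessment continues, and the literal sense of {11d} would end it for an outcome-related reason. Per patient excluded before t1, the additional loss would be 2 of 7 SOMS-7R time points, 2 of 2 later diagnostic interviews, the single NEQ, both safety checks by study personnel, and all post-baseline data on 7 of 9 secondary questionnaires.

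This rests on two assumptions: that a site applies {11d} literally, and that the patient would otherwise have accepted the later assessments. The number of such patients is unknown, and the effect on the primary contrast is probably negligible. What is gained by settling the wording is complete and uniform safety and ITT follow-up across eight centres.

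**What to change.** In {11d}, for randomised patients, replace the exclusion clause with: *will be discontinued from the study intervention; SAE/ESI recording continues, and t1 and follow-up assessments are offered unless consent to data collection is withdrawn*. Exclusion can stay for patients who have consented but are not yet randomised, in line with entry criterion (d).

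The cost is one sentence in the protocol and a note to the eight sites. It adds no procedure beyond those in {11b}, {13} and {22}. Recruitment is planned to run until August 2027, so a clarification now would cover patients still to be treated; assessments that were never made cannot be recovered at the analysis stage.
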